## Abstract

**Objectves::**

The Remote Diet Intervention to Reduce Long COVID Symptoms Trial (ReDIRECT) evaluates whether the digitally delivered, evidence-based, cost-effective Counterweight-Plus weight management programme improves symptoms of Long COVID in people with overweight/obesity.

**Methods::**

Baseline randomised, non-blinded design with 240 participants allocated in a 1:1 ratio either to continue usual care or to add the remotely delivered Counterweight-Plus weight management programme, which includes a Counterweight dietitian supported delivery of 12 weeks total diet replacement, food reintroduction, and long-term weight loss maintenance. Randomisation is achieved by accessing a web-based randomisation system incorporated into the study web portal developed by a registered Clinical Trials Unit. We are using an innovative approach to outcome personalisation, with each participant selecting their most dominant Long COVID symptom as their primary outcome assessed at six months. Participants in the control arm enter the weight management programme after six months. We are recruiting participants from social media and existing networks (e.g., Long COVID Scotland groups), through newspaper advertisements and from primary care. Main inclusion criteria: people with Long COVID symptoms persisting > three months, aged 18 years or above, body mass index (BMI) above 27kg/m
^2^ (>25kg/m
^2^ for South Asians). The trial includes a process evaluation (involving qualitative interviews with participants and analysis of data on dose, fidelity and reach of the intervention) and economic evaluation (within-trial and long-term cost-utility analyses).

**Anticipated results::**

The recruitment for this study started in December 2021 and ended in July 2022. Project results are not yet available and will be shared via peer-reviewed publication once the six-months outcomes have been analysed.

**Trial registration::**

Current Controlled Trials ISRCTN12595520.

## Introduction

After a COVID-19 infection, some people continue to experience long-term effects of the illness known as Long COVID (other names include post-COVID-19 condition, post COVID-19 syndrome, long-haul COVID, and post-acute sequelae of SARS CoV-2 infection (PASC)), a multi-system condition with symptoms which vary from person to person in number, type, severity, and duration. The proportion of people who develop Long COVID remains uncertain – estimates in the UK range from 14% (
Office for National Statistics, 2021) to 38% (REACT-2 Study (
Whitaker *et al.*, 2022)).

Commonly reported symptoms include fatigue, headaches, breathlessness, loss of taste/smell, cognitive dysfunction, and joint and muscle pain (
Davis *et al.*, 2021;
Lopez-Leon *et al.*, 2021;
Sudre *et al.*, 2021) with over 50 long-term effects of COVID-19 reported (
Lopez-Leon *et al.*, 2021). Long COVID presents a major public health issue, with substantial impacts not only on the health service but also individuals and families affected, with substantial impacts on quality of life and economic costs (loss of work, care, and support costs) (
Aiyegbusi *et al.*, 2021;
Michelen *et al.*, 2021;
Vaes *et al.*, 2021). At the time of writing, the pathophysiology of Long COVID is still not well understood. Several underlying disease mechanisms may contribute to different Long COVID symptoms. For instance, research has suggested the following potential contributors: persistent viral infection or reservoir of non-infections remnants; lasting tissue damage due to direct viral toxicity; dysbiosis; small (or ‘micro’) blood clots; auto-immunity; and inflammation following initial infection (
Choutka *et al*., 2022;
Nalbandian *et al.*, 2021;
Phetsouphanh *et al.*, 2022).

Obesity is a risk factor for severe COVID-19 infection, with each additional body mass index (BMI) unit above 23 kg/m
^2^ increasing the risk for a COVID-19 related hospitalisation by 5% (HR 1.05 [95% CI 1.05 – 1.05]) (
Gao *et al.*, 2021). Mendelian randomisation analyses suggest that this link between genetically higher BMI and COVID-19 hospitalisation may be even stronger (OR 1.14 [95% CI 1.07 – 1.21] per additional BMI unit) (
Leong *et al.*, 2021;
Sattar & Valabhji, 2021). Whilst Long COVID can happen following an initial infection at any disease severity, there is evidence suggesting an association between Long COVID and severity of the acute infection: in the COVID-19 symptom study, those who had at least five symptoms in the first week of the acute illness had increased odds of experiencing Long COVID symptoms for more than four weeks (OR 3.95 [95% CI 3.10 – 5.04]) (
Sudre *et al.*, 2021).

Being female and/or living with obesity is associated with lesser likelihood of a full COVID-19 recovery at one year (OR 0·68 and 0·50 respectively) (
Evans *et al.*, 2022). In a meta-analysis of 10 UK longitudinal studies, excess weight (BMI > 25 kg/m
^2^) was associated with increased odds of symptoms lasting for at least four weeks (OR = 1.24, CI 1.01 – 1.53) (
Thompson *et al.*, 2022). In non-hospitalised adults (UK-based primary care data), a higher BMI (>30 kg/m
^2^) was associated with a 10% increased risk of symptoms persisting at least 12 weeks in comparison to those with a BMI in the normal range (adjusted HR 1.10 [95% CI 1.07 – 1.14]) (
Subramanian *et al.*, 2022). In a large community-based sample (REACT-2 study, England), the risk of Long COVID increased with increasing adiposity (overweight: OR 1.15 [95% CI 1.09 – 1.21]; obesity: OR 1.39 [95% CI 1.32 – 1.48]) (
Whitaker *et al.*, 2022).

Potential pathways proposed to link overweight/obesity to more adverse COVID-19 illness include cardiovascular and metabolic impairments, reduced lung function, and a chronic low-grade inflammatory state related to obesity and excess ectopic fat, which may amplify the immune response during COVID-19 infection (
Sattar *et al.*, 2020).

In studies conducted prior to the COVID pandemic, weight loss has been shown to lower inflammatory levels (
Marfella *et al.*, 2004;
Sheu *et al.*, 2008;
Vilarrasa *et al.*, 2007;
Welsh *et al.*, 2010), and may improve cardiometabolic health, lung function, and quality of life (
Aucott *et al.*, 2005;
Avenell *et al.*, 2004;
Stenius-Aarniala *et al.*, 2000). Some of the most common symptoms of Long COVID (fatigue, pains, breathlessness) are also common with overweight/obesity, and helped by weight loss (
Riddle & Stratford, 2013;
Stenius-Aarniala *et al.*, 2000) – there is a need to update the evidence-base to document whether weight management can play a role in Long COVID rehabilitation for people living with excess adiposity. With metabolic complications of obesity (type 2 diabetes (T2D), hypertension, dyslipidaemia) shown to be rapidly reversible with weight loss and loss of ectopic fat (
Aucott *et al.*, 2005;
Lean *et al.*, 2018), weight management is also relevant in the context of increased risk and associated burden of incident diabetes in Long COVID (
Xie & Al-Aly, 2022).

To mitigate the impact of Long COVID, one of the top research priorities identified by a global public forum is to investigate the impact of non-pharmaceutical interventions and anti-inflammatory therapeutics (
Carson & Long Covid Forum Group, 2021). In alignment with this goal, the purpose of the ReDIRECT study is to investigate whether supported weight loss can help alleviate symptoms of Long COVID in people who are living with excess adiposity. ReDIRECT uses an existing dietary weight management programme, shown to be safe, effective, and cost-effective in achieving and sustaining mean weight loss of >15 kg and remission of T2D (Diabetes Remission Clinical Trial (DiRECT)) (
Lean *et al.*, 2018;
Xin *et al.*, 2020).

The ReDIRECT randomised controlled trial, including the diet intervention, is delivered entirely remotely using digital technology. The trial design involves parallel groups allocated in a 1:1 ratio, with a wait-list entry to the weight management intervention for the control group, and a framework to test superiority of the intervention arm. ReDIRECT uses an innovative approach to personalisation, with each participant selecting their dominant symptom as primary outcome. This approach is particularly relevant in the context of the broad spectrum of Long COVID symptoms reported. 

## Study objectives

### Primary research objective

The aim of this research is to implement a remotely delivered digitally supported weight management programme for people with Long COVID, with personalised improvement goals; and to determine the effectiveness and cost-effectiveness of this intervention for improving symptoms.

The primary research objective is to evaluate at six months whether:

1.Effective weight management improves self-selected personalised primary symptoms of Long COVID
*vs* standard care (in absence of established treatment for Long COVID).2.The weight management intervention improves wider health, quality of life and psychological outcomes
*vs* standard care.3.Symptom improvements persist to 12 months.

### Secondary research objectives

1.Assess the implementation of the intervention in terms of dose, fidelity, and reach, and explore differences by sociodemographic characteristics (age, sex, ethnicity, socio-economic status (SES)).2.Explore how contextual factors influence variations in implementation and effectiveness and identify barriers and facilitators to delivery.3.Explore the experience of the intervention from the perspective of participants, including acceptability, patterns of use, and barriers and facilitators to use.4.Evaluate within-trial and long-term cost-effectiveness of the intervention.

## Methods

### Patient and public involvement (PPI)

PPI has been integral to the development of our research. We consulted with people from the Long COVID Scotland support group at an early stage to obtain data on the acceptability and desirability of the ReDIRECT study. A lay co-applicant with lived experience of Long COVID attends Study Management Group (SMG) meetings. We have also established a COVID-19 PPI group, involving people with Long COVID who are independent of the study. The PPI group and lay co-applicant review the ethics application, social media outputs (including the website design), recruitment, analysis and dissemination plans.

### Study design

This registered randomised controlled trial (ISRCTN12595520, protocol registered 25/11/2021) uses a wait-list controlled design, with participants allocated at baseline in a 1:1 ratio to one of two groups using a mixed approach of minimisation (80%) and randomisation (20%). The treatment allocation is performed by a registered Clinical Trials Unit and is designed to maintain balance with respect to the dominant Long COVID symptom (fatigue, breathlessness, pain, anxiety/depression, other), sex (male, female, or other), age (<50, ≥50), self-reported ethnicity using UK Census classifications (White, South Asian, Other) and postcode-based index of multiple deprivation (IMD)) (<median, ≥median).

Participants are randomised to one of two study groups:

Treatment: evidence-based weight management programme (Counterweight-Plus, delivered and supported by Counterweight Ltd)Control: standard care (delayed entry to the Counterweight-Plus programme after six months)

The weight management programme includes a formula low-energy diet for eight to 12 weeks to induce weight loss, food reintroduction and weight loss maintenance (week 8/12 to month six). The impact of the intervention on the patient’s dominant symptom will be assessed at the six-month mark. After six months, observation will continue up to 12 months for cross-sectional analysis of long-term maintenance of weight loss. Participants in the control group will be offered delayed entry to Counterweight-Plus programme at this point and will add observational data to the 12-month time point, but not form part of the RCT analysis (
Figure 1).

**Figure 1. f1:**
[figure not shown]
ReDIRECT trial flow diagram. The ReDIRECT Study is a parallel, non-blinded, wait-list controlled study with 240 participants allocated in a 1:1 ratio either to the Counterweight-Plus weight management programme (treatment) or to continue usual care (control group with delayed entry to the Counterweight-Plus programme after 6 months). The effectiveness of the trial will be evaluated after six months. Further data will be collected after six months to the end of the trial for additional observational analyses. Blue: treatment group (immediate entry to Counterweight); Orange: control group (usual care); CWT: Counterweight; RCT: randomised controlled trial.

The study is open-label due to the nature of the intervention and participants, researchers (who enrol the participants and organise all follow-ups), and dietitians (who deliver the intervention) are aware of the treatment allocation. However, the study statistician will remain blinded to the allocation until completion of the statistical analysis plan and locking of the database up to six months post-randomisation.

There are no pre-specified criteria for discontinuing the intervention or modifying the allocation. The intervention may be discontinued as per a participant’s wishes, or as a result of adverse events making pursuing the intervention incompatible with care. In the event of a participant discontinuing the intervention, participant follow-up remains in place to collect outcome data.

### Setting

All aspects of the study are delivered fully remotely, including recruitment, giving consent, randomisation, the intervention, and outcome assessments to minimise participant burden and cost. Glasgow is the sole study site, whilst participants are recruited across Scotland, England, Wales, and Northern Ireland.

### Study population and recruitment

We aim to recruit a total of 240 people aged 18 years and above, with self-reported symptoms of Long COVID and overweight/obesity (n = 120 per study arm) from general practice, social media, newspaper advertisements and existing networks, such as national Long COVID groups. Inclusion and exclusion criteria are reported in
Table 1. A positive COVID-19 diagnosis is not a requirement for this study due to the unavailability of COVID-19 tests at the start of the pandemic. This inclusive approach was chosen based on feedback from the PPI group and a strong steer from the funder. Reasons for exclusions are fully recorded. There is no exclusion on concomitant care, except when related to the exclusion criteria listed in
Table 1.

**Table 1. T1:** ReDIRECT inclusion and exclusion criteria.

Inclusion criteria	People who are aged **≥**18 years
	People with Long COVID symptoms persisting >3 months before first recruitment contact, not currently hospitalised
	People with a body mass index (BMI) ≥27 kg/m ^2^ (≥25 kg/m ^2^ for South Asians).
Exclusion criteria	People who have had lengthy hospitalisations (>10 days) or intensive care unit admissions related to COVID-19
	People who are currently on insulin or anti-obesity drugs
	People who have had a proven myocardial infarction within the last 6 months
	People with severe mental illness, including severe depression or eating disorder
	Women who are pregnant or considering pregnancy
	People who have a history of substance abuse
	People with an active illness likely to cause a change in weight
	People who underwent bariatric surgery within the last 3 years or are planning bariatric surgery
	People with advanced kidney problems (eGFR < 50 ml/min/1.73m ^2^), gallstones or pancreatitis
	People currently participating in another clinical research trial likely to affect diet or weight change
	People with learning disabilities
	People who are unable to understand English (written or verbal)

Recruitment from general practice is facilitated by the NRS Primary Care Network using electronic records search, with potential participants sent an invitation to participate from their GP on behalf of ReDIRECT, including a participant information sheet explaining the study.

The social media strategy includes regular posts and activity on Twitter and Facebook on behalf of the ReDIRECT Study. Prospective participants are to be directed to the study website and to contact the research team via email. In addition, existing groups and organisations have been identified to support dissemination within their networks. We are working with community stakeholders to increase representation of minorities / usually under-represented groups.

Posters have been placed in primary care waiting rooms to remind patients and encourage those interested to respond if they had received an invitation. Patients who respond as interested in participating are contacted by a member of the research team and invited to attend for a remote screening appointment where the study is fully explained and discussed. Informed consent is secured by the study researchers from all participants, as per trial protocol and for optional indefinite long-term data collection from their medical records and through national records linkages. Participant information sheets and consent forms are sent and returned by emails, initialled and signed (documents available on the ReDIRECT study website
https://redirectstudy.co.uk/publications/).

Recruitment began in December 2021 and was completed in July 2022.

### Weight management programme

The format and support of the intervention is delivered remotely by the evidence-based Counterweight-Plus Programme (
Lean *et al.*, 2018). All support is delivered by registered dietitians. Counterweight-Plus is a structured intervention utilising total diet replacement (TDR), and behaviour change to help people lose at least 15 kg (or 15% of their body weight if over 100 kg) and keep it off long term. Recognising that fatigue and mobility difficulties are frequent among people living with Long COVID and among those living with obesity, the programme is delivered to participants’ homes and supported entirely remotely and patient-reported outcomes are used to maximise acceptability and protocol adherence.

The programme runs for 12 months and is divided into two phases:

### Weight loss induction phase (from week 0 to week 8–12)

Counterweight provides 8–12 weeks of a low-energy, nutritionally complete, formula diet (850 kcal/day) to replace all meals (total diet replacement, TDR), aiming for ≥15 kg (or 15% of their body weight if over 100kg) weight loss. Products include a variety of soups and shakes provided free of cost to the participant. Those who are unable, or prefer not to, follow the TDR formula diet (10% in the published DiRECT study (
Lean *et al.*, 2018)) are offered an alternative approach providing 1200 kcal/day, either a meal replacement diet in which a maximum of two meal replacements are consumed per day or a food-based low-carb or low-fat approach. Food used to supplement the TDR or for fully food-based plans is purchased by the participants and not provided by the study. To increase adherence to the programme, support is tailored to individual participants, allowing for flexibility around commitments or life events. Further strategies are pre-emptively discussed, e.g., the possibility of adding in one meal/day or including ‘days off’, with encouragement to resume the full TDR at subsequent visits and to maintain whatever weight has already been lost and moving onto the maintenance phase early if necessary to avoid dropping out altogether.

### Weight loss maintenance phase (week 8/12 – six months)

Food is reintroduced stepwise while reducing TDR. The transition period to a full food-based diet lasts between 4–12 weeks (usually eight weeks) and is individualised to participants. A management plan will be provided along with support for standard evidence-based behaviour change techniques, including self-monitoring of behaviours and behavioural outcomes, goal-setting and self-rewards, action planning, and problem solving. During this time, participants measure their weight weekly and enter this into the Counterweight App to monitor progress with weight loss maintenance.

Relapse treatments are available for >2 kg weight gain. These include reinforcing behaviour change techniques and the option to return to TDR, a 1,200-kcal meal replacement diet, or a 1,200-kcal low carb or low-fat diet for two weeks. Alternative evidence-based dietary strategies are considered on an individual basis (intermittent or alternate-day fasting, time-restricted eating).

Counterweight dietitians provide personalised support throughout the 12-month intervention via text chat, video or telephone, in-app weekly monitoring, nudges, and personalised messaging. Remote appointments are offered on a monthly basis, following initiation into the programme, however, these appointments are flexible to the needs of individuals.

Group support is facilitated using group text chat, and a Facebook community for all Counterweight users.

### Medication review

Each participant is asked to report any prescribed medications at baseline. The Counterweight team follows the published medication withdrawal and reintroduction protocol as used in the DiRECT study. Weight loss is likely to result in a reduction of blood glucose levels and blood pressure. As a safety measure to avoid hypoglycaemia and postural hypotension, it is recommended that all anti-diabetic, anti-hypertensive, and diuretic medication should be stopped on the day TDR is commenced. Blood glucose levels and blood pressure are monitored at each review appointment and, if necessary, medication is reintroduced following a defined protocol. Any such actions, as well as observations and intervention results, which may pose a risk to the participant’s health are discussed between Counterweight dietitians, the participant, and the participant’s general practitioners (GPs). In addition, study clinicians are on hand to provide supplementary advice and guidance regarding participant medication where required.

### Study outcome measures

Outcomes are all measured for both groups at baseline, three, and six months. Follow-ups for cross-sectional analysis are measured at 12 months in the treatment group and nine, 12, and 18 months for the control group, with the exception of height, which is recorded at baseline only.

Due to geographical constraints for this UK-wide trial coupled with COVID-19 constraints, all trial outcomes are self-reported, using a bespoke electronic case report form (eCRF). Remote measurement is anticipated to minimise participant burden and cost and to maximise retention. To facilitate self-reported measurements of weight and blood pressure, participants receive digital scales (Model UC-502, A&D Instruments Ltd, Abingdon, UK) and fully automatic blood pressure monitors (arm type monitor TMB-1970, Kinetik Medical Devices Ltd, Redhill, UK) by post. Other measurements are collected through the eCRF / web-based questionnaires, with all entries verified by the study researchers, who are available to liaise and assist participants throughout the study.

### Primary and secondary outcome measures

All participants are asked to fill in online questionnaires related to a range of identified Long COVID outcomes (
Table 2). The primary outcome is a continuous measure derived from the symptom score for the self-selected dominant Long COVID symptom, nominated by each participant at baseline.

**Table 2. T2:** ReDIRECT trial outcome measures.

	Primary outcome measures	Scales / Tools	References
Self-selected Long COVID symptom	Fatigue	Validated Chalder Fatigue Scale CFQ-11	( Chalder *et al.,* 1993)
	Breathlessness	Modified MRC Dyspnoea Scale	( Bestall *et al.,* 1999)
	Pain	P4 Numeric Pain Rating Scale	( Spadoni *et al.,* 2003)
	Anxiety and depression	Hospital Anxiety and Depression Scale (HADS) questionnaire	( Zigmond & Snaith, 1983)
	Other	Visual Analogue Scale (0-10) for other symptoms with no pre-specified scale	
	Secondary outcome measures	Scales / Tools	References
All non-selected primary Long COVID symptoms	Fatigue, breathlessness, pain, anxiety/depression, other	As above	As above
Body composition and health	Weight	Digital scales (Model UC-502, A&D Instruments Ltd, Abingdon, UK)	
	Height		
	Blood pressure	Arm type monitor (TMB-1970, Kinetik Medical Devices Ltd, Redhill, UK)	
	COVID vaccination		
	Medication		
Other	Quality of life	EQ-5D 5L	( Buchholz *et al.,* 2018)
	Work productivity	Work Productivity and Activity Impairment	( Reilly *et al.,* 1993)
	Healthcare utilisation	Bespoke questionnaire	
	Food expenditure	Bespoke questionnaire	

Secondary outcome measures include all non-selected primary Long COVID symptom outcomes (fatigue, breathlessness, pain, anxiety/depression, other), as well as weight and blood pressure (both self-measured using equipment provided and self-reported via the online questionnaire at assessment timepoints), and other health and wellbeing outcomes outlined in
Table 2.

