### Statistical analysis

At the design stage for the trial, the primary outcome was proposed as the self-selected, most troublesome symptom (fatigue, breathlessness, pain, anxiety/depression, or another symptom as selected by the participant). Since each outcome measure will have a different distribution, the proposal was to standardise each measure by subtracting the mean and dividing by the standard deviation (SD) from those participants who selected that symptom as their most troublesome. The suitability of this measure for the primary analysis will be assessed during the trial, as data accrue, in blinded analyses. Reports to the Trial Steering Committee (TSC) include assessments of the distribution of this measure, and the committee will advise and approve the final choice of primary outcome and its analysis. The TSC will approve the final Statistical Analysis Plan, prior to locking the six-months dataset and unblinding the statistical team.

The proposed analysis of the primary outcome at six months will be to compare randomised groups using a linear regression model, adjusting for the baseline value of the primary outcome, and factors used to balance the randomisation/minimisation procedure. We do not plan interim analyses. The intervention effect will be reported as the adjusted mean difference between groups, with a 95% confidence interval, and p-value. The analysis will be according to the intention-to-treat principle, in that participants will be analysed according to their randomised group, regardless of compliance with the intervention.

Secondary analyses will use linear or logistic regression, as appropriate, to estimate between-group differences or odds ratios for secondary outcomes. Missing data will not be imputed initially, but the sensitivity of main analyses will be explored using multiple imputation, and analyses weighted by the inverse probability of follow-up, based on a non-parsimonious model of the probability of being followed up, as a function of baseline characteristics. Associations between baseline characteristics, primary and secondary outcomes will be explored by extending the main analysis regression models.

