Evans *et al.*, 2022). In this study, we aim to establish the impact of intentional weight loss on Long COVID symptoms in people living with excess adiposity. There are no current nutritional recommendations for patients with Long COVID, with uncertainty surrounding the suitability of physical activity and dietary approaches in Long COVID (
Barrea *et al.*, 2022). Weight management may benefit Long COVID patients with overweight or obesity in several ways. In the context of obesity and overweight, weight reduction has well described cardiovascular and renal effects (
Cohen & Cohen, 2015). Weight reduction also improves inflammation (
Forsythe *et al.*, 2008). Weight loss has also been shown to improve quality of life, more so in those living with greater excess weight, and to reduce symptoms common to both being overweight and Long COVID, such as fatigue, breathlessness, and pain (
Babb *et al.*, 2011;
Buckell *et al.*, 2021;
De Lorenzo *et al.*, 1999;
Malfliet *et al.*, 2021;
Rigamonti *et al.*, 2020).

The weight management programme adapted in this research has proven health benefits in the general population and in world-leading research on remission of T2D – a co-morbidity of obesity and the second most common co-morbidity of COVID-19 (after hypertension) (
Singh *et al.*, 2020). The programme, Counterweight-Plus, has already been subjected to both feasibility and full-scale randomised controlled trials, and was successfully adopted for the Diabetes Remission Clinical Trial (DiRECT) (
Lean *et al.*, 2018).

The dominant symptom of Long COVID is fatigue (

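### Symptom scales are secondary outcomes only where not selected, so no listed analysis gives each scale's effect in its own units across all randomised participants

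*Protocol article*

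**What the plan says.** In the protocol article, the section on primary and secondary outcome measures sets the primary outcome participant by participant: "The primary outcome is a continuous measure derived from the symptom score for the self-selected dominant Long COVID symptom, nominated by each participant at baseline". It then gives the symptom secondary outcomes: "Secondary outcome measures include all non-selected primary Long COVID symptom outcomes (fatigue, breathlessness, pain, anxiety/depression, other"). The matching row of Table 2 reads "All non-selected primary Long COVID symptoms". No row or sentence lists the CFQ-11, the modified MRC scale, the P4 or the HADS as an outcome in all randomised participants.

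On data collection, the same section says "All participants are asked to fill in online questionnaires related to a range of identified Long COVID outcomes", and the section on study outcome measures says "Outcomes are all measured for both groups at baseline, three, and six months".

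On analysis, the Statistical analysis section proposes to standardise the selected symptom's score by subtracting the mean and "dividing by the standard deviation (SD) from those participants who selected that symptom as their most troublesome". For the rest it says: "Secondary analyses will use linear or logistic regression, as appropriate, to estimate between-group differences or odds ratios for secondary outcomes". It gives no analysis set for any individual scale. Main symptom is one of the prespecified subgroups. Under Study design, dominant symptom is one of the factors balanced by the minimisation.

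**The concern.** Selection is made by each participant, so a restriction to non-selected symptoms changes who is in each comparison. Fatigue is a secondary outcome only for those who did not choose fatigue, pain only for those who did not choose pain, and so on. Each scale then has its own population, and each omits the people for whom that symptom matters most to them.

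The omitted scores appear elsewhere only as part of a standardised measure pooled over symptoms. A clinician asking how many CFQ-11 points the programme changes fatigue by, in the people randomised, would find no listed analysis that answers. The gap is widest for the symptom chosen most often. The Discussion suggests which one that may be: "The dominant symptom of Long COVID is fatigue".

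The entry for other symptoms raises a separate difficulty. Its visual analogue scale is meant for symptoms that have no scale of their own. The article does not say what a participant who selected one of the four named symptoms would rate on it, so a non-selected other symptom is not clearly defined.

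**Working it through.** **1. Reproduce the stated sample size.** Inputs from the Sample size section: difference 0.5, SD 1, 5% significance, 90% power. Two-sided testing is assumed, since sidedness is not stated.

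n per arm = 2(1.960 + 1.282)² / 0.5² ≈ 84.1, rounded up to 85. The t-test version gives 85.03, rounded up to 86. The stated 86 per arm is reproduced. Power at 86 is 90.6% (normal approximation) or 90.3% (t-test). This figure concerns the primary outcome and is not affected by the point made here.

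**2. Effect of the restriction.** Let f be the share who select a given symptom. The article does not give f, so the values below are assumptions. With 86 per arm followed up and SD 1 on each scale:

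- number left per arm: m = 86(1 − f)
- standard error of the difference: √(2/m)
- inflation relative to using everyone: 1/√(1 − f)
- power for 0.5 SD: Φ(0.5√(m/2) − 1.960)

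| Share selecting, f | m per arm | Standard error | Inflation | Power for 0.5 SD |
|---|---|---|---|---|
| 0 (everyone) | 86 | 0.152 | 1.00 | 90.6% |
| 10% | 77.4 | 0.161 | 1.05 | 87.5% |
| 30% | 60.2 | 0.182 | 1.20 | 78.3% |
| 50% | 43.0 | 0.216 | 1.41 | 64.0% |
| 70% | 25.8 | 0.278 | 1.83 | 43.5% |

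The inflation column does not depend on attrition. With all 120 per arm followed up and f = 50%, 60 per arm remain and power is 78.2%.

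The shares over the five symptom categories sum to 100%, so at most one category can exceed 50%. The lower rows can apply to one scale, not to all of them.

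The power column is for scale only. The protocol claims no power for secondary outcomes. The calculation also takes the same SD in selectors and non-selectors and ignores the gain from baseline adjustment.

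**3. Is the restricted comparison biased?** Selection is made at baseline, before allocation, and is a minimisation factor. Non-selectors of a symptom are therefore a baseline-defined subset in which the arms remain comparable by randomisation. The restriction costs precision and changes the population. It does not introduce confounding.

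**4. Where do the selectors' scores go?** They form the primary outcome, and the main-symptom subgroup analysis gives an effect within selectors. Both are in SD units as planned. Neither combines selectors and non-selectors on one scale.

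**The case against.** The strongest reply is that the article states no exclusion. It sorts outcomes into primary and secondary for each participant, uses the open word *include*, and sets no analysis set for any scale. The SAP is not shown and could analyse each scale in everyone. This stands in part: the omission of selectors is inferred from the outcome definition and is not written as a rule. But the restriction appears in both the text and the table, and *include* leaves room for further outcomes without removing the qualifier on this one. A SAP that follows the protocol inherits the restriction, and one that analyses everyone departs from it.

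A second reply is that nothing is lost, because selectors' scores feed the primary outcome and the subgroup, and multiplying a subgroup effect by its SD returns it to scale units. That is right as far as it goes. It yields an effect among selectors, not in the whole randomised population.

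A third reply is that keeping the two sets apart avoids reporting one score as both primary and secondary. That is a legitimate reason, but noting the overlap deals with it.

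A reader might also infer that data are discarded, that the most severely affected are removed from each scale, or that floor effects follow. The documents do not support this. The scores are used in the primary analysis. Participants nominate a dominant or most troublesome symptom, which need not be their highest score, and someone with severe fatigue may nominate pain. No score distributions are given.

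**Conclusion.** The point holds as a matter of outcome definition. As written, the symptom secondary outcomes cover non-selectors only, and no listed analysis estimates the effect on each named scale, in its own units, across the randomised population. The comparison that is listed is valid but smaller and less general than the data allow.

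The size depends on a selection share that the article does not give. The standard error is about 5% larger at 10% selecting and 41% larger at 50%, so the matter is minor for rarely chosen symptoms and material for the commonest. These figures assume SD 1 on each scale, the same in selectors and non-selectors. The power figures should not be read as a shortfall against a promise, because none was made for secondary outcomes.

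**What to change.** Reword the outcome section and Table 2 so that CFQ-11, modified MRC, P4 and HADS scores at six months are secondary outcomes in all randomised participants. Compare arms by linear regression adjusted for the baseline score of that scale and the minimisation factors, which include dominant symptom. Show the selector and non-selector estimates as a supplementary display. Analyse the visual analogue scale for other symptoms only in those who nominated and scored such a symptom at baseline.

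The cost is wording in the protocol and SAP; for the four named scales no further data collection is planned for or needed. The article has the Trial Steering Committee approve the final SAP before the six-month dataset is locked and the statistical team unblinded, so the change can be settled at that step. The one downside is that a selector's score on the chosen scale also feeds the primary outcome. The secondary results will be correlated with the primary result, and the report should say so.
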